**Methods:**

At least 68 patients diagnosed with HAND will be randomly placed into either an aerobic exercise group or control group. Patients in the aerobic exercise group will perform a moderate intensity workout on a stationary bicycle ergometer, 3 times a week for 12 weeks. We will measure the primary outcomes including neurocognitive performance, prevalence of HAND, viral load, and CD4 count. We will evaluate postexercise neurocognitive performance using reliable neuropsychological tests relevant to people living with HIV, in line with the Frascati criteria. We will assess secondary outcomes such as quality of life, activity limitation, and social participation using the World Health Organization Quality of Life (WHOQOL)-Brief, and the Oxford Participation and Activities questionnaire. We will use exploratory statistics to test the data for normality and homogeneity. We will analyze the effect of the exercise program on HAND using relative risk (RR) and absolute risk reduction (number needed to treat). Analysis of covariance will be run to estimate the effect of exercise on quality of life and activity and participation level.

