### Participant Timeline

The proposed timeline for the study and planned elements is shown in Figure 1. All prospective participants were identified in a pilot study. Baseline assessments were conducted from the end of January 2021 to mid-February 2021 and covered neurocognitive performance, BP, HR, respiratory rate, assessment of physical activity readiness, QoL, CD4 count, viral load, and activity limitation and social participation. Before the intervention, all participants undergo an exercise stress test. The aerobic exercise intervention starts a day after exercise testing and lasts for 12 weeks. Following the 12-week aerobic intervention, postexercise assessments are conducted.

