#### The WHO Quality of Life-BREF

We use the short form of the World Health Organization Quality of Life (WHOQOL)-BREF, which has been validated in diverse settings, including African countries, and is based on a well-classified definition of QoL (Multimedia Appendix 10). It is comprised of physical, psychological, social, and environment domains. The WHOQOL-BREF is a recommended instrument for people living with HIV infection [69,70]. The WHOQOL-BREF has an internal consistency of α=0.74-0.85 and test-retest reliability of rho=0.64-0.79 [71]. Each of the 4 domains is measured on a 5-point Likert scale: 1 indicates low perception, and 5 indicates high perception [69]. The WHOQOL-BREF measures the perceived QoL and hence contains items asking how patients felt about different facets of life in the week before being assessed.

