### Statistical Methods

Primary and secondary variables will be tested for normality and heterogeneity using Kolmogorov-Smirnov and Levene tests, respectively. We will compare the control group and exercise group using a 2-way analysis of variance with repeated measurements and Bonferroni correction. Primary outcome measures are cognitive performance, QoL, activity limitation, and participation. We will compute hazard ratios to evaluate the effect of the intervention over time. SPSS version 21 (IBM Corp, Armonk, NY) will be used.

We expect that potential confounding variables, not accounted for by randomization, may influence outcomes between the control and study groups. We will include potential confounding variables in appropriate analysis of covariance. Covariates include neurocognitive performance test scores (clinical rating algorithm), CD4 count (classified as <350 cells/µl or ≥350 cells/µl), viral load (classified as detectable [>400 copies/mL] or undetectable [<400 copies/mL]), age, sex, level of education, BMI, exercise adherence (classified as nonadherent [≤40%] or adherent [>40%]), adherence to ART since the intervention (classified as nonadherent [≤40%] or adherent [>40%]), ART regimen, ovulation, and vaccination status. Also, our findings will be included in an updated meta-analysis of the effects of exercise on cognition in people living with HIV to understand how the study outcome may drive existing associations. The initial meta-analysis was conducted by our team [43].

As per nonadherence to a study protocol, we will employ intention-to-treat analysis. Effort will be made to prevent missing data through cross-checking of the information obtained from participants. In case of missing data, we will explore patterns of missing and, where appropriate, multiple computation will be executed using SPSS version 21.

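### The covariate list for the ANCOVA of quality of life and activity/participation does not name the baseline value of the outcome being analysed, an avoidable loss of precision

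*Protocol article*

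**What the plan says.** The Methods paragraph of the abstract gives these outcomes their effect-estimating model: "Analysis of covariance will be run to estimate the effect of exercise on quality of life and activity and participation level".

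Statistical Methods states what the covariates are for: "We will include potential confounding variables in appropriate analysis of covariance". The list then opens with "Covariates include neurocognitive performance test scores (clinical rating algorithm), CD4 count", continues with "viral load (classified as detectable [>400 copies/mL] or undetectable [<400 copies/mL]), age, sex, level of education, BMI, exercise adherence", adds ART adherence, and ends with "ART regimen, ovulation, and vaccination status". That makes twelve variables, several with their cut-points. No WHOQOL-BREF or Ox-PAQ baseline score is among them, and no other section says that an outcome's own baseline enters its model.

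Participant Timeline includes both outcomes in the baseline assessment: "QoL, CD4 count, viral load, and activity limitation and social participation". Study Outcomes plans measurement at baseline, after 12 weeks and 3 months after the intervention.

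The other planned group comparison is a "2-way analysis of variance with repeated measurements and Bonferroni correction".

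**The concern.** The baseline value of a questionnaire is normally the strongest single predictor of its value at follow-up. The list spends degrees of freedom on ovulation and vaccination status in a trial of 68, yet does not name that predictor. The variables were chosen as potential confounders, a principle that would not bring in the outcome's own baseline by itself.

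The stake is precision. An analyst who fits the list as printed gets a wider confidence interval than the collected data allow, for outcomes that Statistical Methods counts as primary (Study Outcomes lists them as secondary). If baseline adjustment is not written down, whether to use it also remains a choice that could be made after the data are seen.

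**Working it through.** **The plan's own figure.** Sample Size gives a difference of 13.4, SD 16.67, two-sided 5% and 34 per group. The standardised difference is 13.4/16.67 = 0.804. The exact noncentral t gives power 0.904 at 34 per arm and 0.895 at 33, so 34 per arm reproduces. This is an unadjusted t test on a scale that the section does not name. The arm size is used below; the 0.804 is not taken as an effect on quality of life or Ox-PAQ.

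**Inputs**
- 34 per arm, two-sided 5% (Sample Size).
- Correlation ρ between baseline and follow-up score: not given. Assumed range 0.4 to 0.79. The upper part is borrowed from the WHOQOL-BREF section, "test-retest reliability of rho=0.64-0.79", which is a reliability with no interval stated and not a 12-week correlation in this population. No value is given for Ox-PAQ.
- Effect of 0.5 SD: an illustration, not a protocol figure.

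**Residual variance**, in units of the outcome variance, with equal variances at both visits:
- follow-up score only: 1
- change from baseline (the group-by-time contrast of a repeated-measures ANOVA with two time points): 2(1 − ρ)
- follow-up score adjusted for baseline: 1 − ρ²

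The protocol does not state the dependent variable of the ANCOVA, so both comparators are needed.

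**Reduction in standard error from adding the baseline**
- against follow-up only: 1 − √(1 − ρ²)
- against change: 1 − √[(1 − ρ²)/(2(1 − ρ))] = 1 − √[(1 + ρ)/2]

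| ρ | 1 − ρ² | 2(1 − ρ) | SE reduction vs follow-up only | SE reduction vs change |
|---|---|---|---|---|
| 0.40 | 0.840 | 1.20 | 8% | 16% |
| 0.64 | 0.590 | 0.72 | 23% | 9% |
| 0.79 | 0.376 | 0.42 | 39% | 5% |

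**Power for 0.5 SD at 34 per arm.** Noncentrality is 0.5/√(v × 2/34), where v is the residual variance above. Degrees of freedom are 66, or 65 with the baseline covariate. For follow-up only, 0.5/√(2/34) = 2.06, which gives 53%.

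| ρ | Follow-up only | Change score | Baseline-adjusted |
|---|---|---|---|
| 0.40 | 53% | 46% | 60% |
| 0.64 | 53% | 67% | 75% |
| 0.79 | 53% | 88% | 91% |

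**Equivalent sample size.** Against follow-up only, 68/(1 − ρ²) gives 81, 115 and 181. Against change, 68 × 2/(1 + ρ) gives 97, 83 and 76.

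No other covariate is in any of these models. If cognition, education or other listed variables already explain part of the outcome, the added gain is smaller, so each figure is an upper one for its ρ.

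**The case against.** The case against has several parts.

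- **The list is open.** It opens with a form of the verb include, is one pool for all outcomes, and is offered for confounders. An outcome's own baseline is a matter of model form that a fuller document might fix. It stands that baseline adjustment is not excluded. But this list is detailed down to cut-points and variables of minor expected value, and an analyst working from it would not be led to add the baseline.
- **The model need not be follow-up only.** A reader might infer that the ANCOVA compares follow-up scores alone, and that the trial therefore moves from 53% to 75%–91% power by adding the baseline. The text does not support this as the plan's position: no section states the dependent variable, and a change score is equally compatible. Against a change score, the gain at correlations of 0.64 and 0.79 is 67% to 75% and 88% to 91%. Precision is still lost under either reading.
- **The repeated-measures ANOVA uses the baseline.** A reader might infer that chance imbalance between the arms goes wholly uncorrected. It does not: the group-by-time contrast compares changes from baseline. This stands, although that contrast is less efficient than baseline-adjusted ANCOVA and is a different model from the one the abstract assigns to these outcomes.
- **The correlation is borrowed.** This stands, and is why a lower value of 0.4 is shown.

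Two extensions are also tempting and lack support. The protocol does not assign ANCOVA to maximum oxygen uptake, so the point does not cover it. Nor does anything here show that cognition, CD4 count or viral load should leave the models.

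**Conclusion.** The point holds as an avoidable loss of precision in the ANCOVA of quality of life and of activity/participation. For correlations assumed between 0.4 and 0.79, naming the baseline outcome cuts the standard error by about 8% to 39% if the model otherwise uses follow-up scores alone, and by about 16% to 5% if it otherwise compares changes. The sizes rest on that assumed range, on equal variances at both visits and on no overlap with the listed covariates.

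The analysis is not invalid: the omission biases nothing by design in a randomised comparison, and the stated sample size is correct for its unadjusted t test. The change is worth making because it has no real downside.

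**What to change.** In Statistical Methods, add a sentence stating that the ANCOVA of each of these outcomes includes, as a continuous covariate, the baseline value of that same outcome: the baseline WHOQOL-BREF score in the quality-of-life model and the baseline Ox-PAQ score in the activity/participation model. The same sentence should name the dependent variable and the visit being tested.

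The cost is one sentence and one degree of freedom per model. The scores are already collected, and the article reports that data analysis had not yet been carried out, so at that point the change could still be prespecified.

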### Study Outcomes

The primary outcomes include neurocognitive performance, prevalence of HAND, viral load, and CD4 count. The secondary outcomes include maximum oxygen uptake (VO_2_), QoL, activity limitation, and participation restriction. Potential confounding variables include age, sex, level of education, vaccination, history of virologic failure, level of ART adherence, exercise adherence, ART regimen, ovulation status, history of recent vaccination, and seasonality. These variables will be measured at baseline, after 12 weeks, and 3 months after the intervention. Their change will be measured over time. Aggregation parameters will include proportion, mean, or median depending on how the data are distributed.

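### CD4 count and viral load enter the analysis of covariance only as two-class variables with no time point: a small loss for quality of life and participation, a material one only if CD4 itself is analysed this way

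*Protocol article*

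**What the plan says.** Statistical Methods states: "We will include potential confounding variables in appropriate analysis of covariance". The covariate list that follows includes "CD4 count (classified as <350 cells/µl or ≥350 cells/µl") and "viral load (classified as detectable [>400 copies/mL] or undetectable [<400 copies/mL"]). No continuous form of either marker is mentioned. In the same list, age and BMI carry no classes and neurocognitive performance enters as a score.

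Four other statements bear on the point:

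- Study Outcomes: "The primary outcomes include neurocognitive performance, prevalence of HAND, viral load, and CD4 count". On timing it adds: "These variables will be measured at baseline, after 12 weeks, and 3 months after the intervention". The Participant Timeline confirms that CD4 count and viral load were part of the baseline assessment.
- Statistical Methods gives a different primary list: "Primary outcome measures are cognitive performance, QoL, activity limitation, and participation". Neither marker is in it.
- The abstract's Methods paragraph: "Analysis of covariance will be run to estimate the effect of exercise on quality of life and activity and participation level".
- Statistical Methods, on the group comparison: "We will compare the control group and exercise group using a 2-way analysis of variance with repeated measurements and Bonferroni correction".

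**The concern.** Adjusting for a baseline covariate removes the part of the outcome variance that the covariate explains and corrects chance imbalance between the arms. Cutting the covariate in two discards part of both benefits, because everyone on the same side of the cut is treated as identical. The loss matters most when the covariate is the baseline value of the outcome itself, since that correlation is usually the strongest available.

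The missing time point adds to this. The covariate list mixes kinds of variable: exercise adherence and ART adherence since the intervention arise after randomisation. The reader therefore cannot be sure from the list alone that CD4 and viral load are baseline values.

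At stake is precision in whichever analyses use these covariates. The cut points are printed in the article, so this is a stated choice and not a detail left to a fuller plan.

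**Working it through.** **The plan's own figure.** Sample Size gives 34 per group for 90% power, difference 13.4, SD 16.67, two-sided 5%, two-group t test. The standardised difference is 13.4/16.67 = 0.804. The noncentral t distribution gives power 0.895 with 33 per group and 0.904 with 34, so 34 per group (68 in total) is reproduced. No covariate enters this calculation.

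**Inputs not in the documents (assumed).** The correlation r between the continuous covariate and the outcome, taken as 0.3 to 0.8. The share p of participants below the cut, taken as 5% to 50%. A normally distributed covariate.

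**Formulas.** Relative to an unadjusted comparison, residual variance is

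- continuous covariate: 1 − r²
- two-class covariate: 1 − k·r², with k = φ(z_p)² / [p(1 − p)]

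Here k is the share of the variance reduction that survives the split. At the median, φ(0)² = 0.159 and k = 0.159/0.25 = 0.637, which is the largest value k can take.

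**Variance ratio, two-class over continuous: (1 − k·r²)/(1 − r²)**

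| Share below cut | k | r = 0.3 | r = 0.5 | r = 0.7 | r = 0.8 |
|---|---|---|---|---|---|
| 50% | 0.637 | 1.04 | 1.12 | 1.35 | 1.65 |
| 30% | 0.576 | 1.04 | 1.14 | 1.41 | 1.75 |
| 20% | 0.490 | 1.05 | 1.17 | 1.49 | 1.91 |
| 10% | 0.342 | 1.07 | 1.22 | 1.63 | 2.17 |
| 5% | 0.224 | 1.08 | 1.26 | 1.75 | 2.38 |

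Example at r = 0.7, median split: (1 − 0.637 × 0.49)/(1 − 0.49) = 0.688/0.51 = 1.35.

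The r = 0.3 column stands for CD4 as a weak covariate for another outcome such as quality of life. The columns from 0.5 upwards stand for CD4 as the covariate for its own follow-up value.

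**In terms of power.** Take 34 per arm and an assumed standardised effect of 0.5, with power = Φ(0.5·√(34/2)/s − 1.96), where s is the square root of the residual variance factor. Unadjusted power is 0.54. At r = 0.7 it is 0.66-0.70 with the two-class covariate (20% to 50% below the cut) and 0.82 with the continuous one. At r = 0.3 it is 0.56-0.57 against 0.58.

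**Repeated-measures comparison.** With one baseline and one follow-up value of equal variance, the group-by-time test is a change-score comparison with variance factor 2(1 − r). Against continuous ANCOVA the ratio is 2(1 − r)/(1 − r²) = 2/(1 + r): 1.33 at r = 0.5, 1.18 at 0.7 and 1.11 at 0.8. This is a simplification, since the article plans a third measurement.

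**The case against.** The strongest reply is that no ANCOVA with CD4 or viral load as the outcome is set out anywhere. The abstract ties ANCOVA to quality of life and activity/participation, and Statistical Methods names no outcome for it. The stated group comparison is a repeated-measures ANOVA, and nothing says the markers are split there; an uncut baseline CD4 would enter as one of the repeated measurements. This stands, and it is why the larger figures are conditional. It does not remove the point: Statistical Methods excludes no outcome from ANCOVA, and the split is inefficient, if only slightly, for the outcomes the abstract names.

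A reader might infer that a primary analysis of CD4 is already fixed with a split baseline. The documents do not support that. No such model is stated, the covariates carry no time point, and the two lists of primary outcomes disagree on whether CD4 and viral load are primary at all. That disagreement is a separate matter.

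A reader might also infer that the trial loses planned power, for instance that 68 participants are worth only about 50 (68/1.35) at r = 0.7. That figure is measured against an ideal continuous ANCOVA. The sample size assumes no adjustment, and even a two-class covariate brings residual variance below that basis, so no planned power is lost.

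For viral load the normal model is poor. If most participants are suppressed, a detectable/undetectable split may lose little, so the numerical case rests on CD4.

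Finally, a condensed article may leave to a fuller plan which covariates enter which model. That is fair for the scope of the ANCOVA, but not for cut points that the article itself prints.

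**Conclusion.** The point holds in a limited, conditional form. The article specifies CD4 and viral load as two-class ANCOVA covariates without a time point, although continuous baseline values exist, and its viral load classes omit exactly 400. Under normality the split forfeits at least 36% of the variance reduction the continuous covariate would give (1 − 0.637).

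- For the outcomes the abstract ties to ANCOVA, the variance cost is about 4-8% at an assumed r of 0.3.
- If CD4 is also analysed by ANCOVA, residual variance would be about 12-65% larger than with continuous baseline CD4, at an assumed r of 0.5-0.8 and a median split. It would be larger still if 350 lies far from the median.

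Neither r nor the share below 350 is given in the documents. That the covariates are baseline values is a reasonable inference, since they are described as confounders that randomisation may leave unbalanced, but it is not stated. The sample size of 68 is unaffected.

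**What to change.** In Statistical Methods:

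1. State that the CD4 and viral load covariates are the baseline values.
2. Enter CD4 as a continuous variable, transformed if its distribution requires it, and viral load as log10, with an indicator for undetectable if many values lie below the limit.
3. Name the outcomes analysed by ANCOVA, and adjust each continuous one for its own baseline on a continuous scale.
4. Keep the 350 and 400 classes for descriptive tables only, and assign a value of exactly 400 to one of the two classes.

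No new data are needed, and the Results section reports that analysis had not begun. The cost is slight: a transformation to choose in advance and one possible extra model term.

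### The ANCOVA adjusts for exercise adherence and post-intervention ART adherence, so its arm coefficient is not the intention-to-treat effect the protocol promises

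*Protocol article*

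**What the plan says.** The Statistical Methods section of the protocol article first plans a two-way repeated-measures ANOVA to compare the groups, with no covariates named. It then turns to adjustment: "We will include potential confounding variables in appropriate analysis of covariance". The covariates that follow include "exercise adherence (classified as nonadherent [≤40%] or adherent [>40%]), adherence to ART since the intervention", with ART adherence cut at the same 40%. The Study Outcomes section lists among its potential confounders "level of ART adherence, exercise adherence, ART regimen, ovulation status".

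The abstract gives the ANCOVA an estimating role: "Analysis of covariance will be run to estimate the effect of exercise on quality of life and activity and participation level". The Statistical Methods section counts quality of life, activity limitation and participation as primary outcome measures. The Study Outcomes section makes them secondary, which is a separate inconsistency. The Statistical Methods section also commits to an intention-to-treat analysis.

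The same covariate list begins "Covariates include neurocognitive performance test scores (clinical rating algorithm), CD4 count (classified as <350 cells/µl or ≥350 cells/µl), viral load". These three are primary outcomes in the Study Outcomes section ("The primary outcomes include neurocognitive performance, prevalence of HAND, viral load, and CD4 count"), and the covariate list gives no time point for them.

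**The concern.** A confounder of a randomised comparison would have to precede allocation. Exercise adherence cannot: it records how much of the assigned treatment was taken. ART adherence is, by the protocol's own wording, counted from the intervention onward, so it is also post-randomisation and may respond to the intervention.

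Holding exercise adherence fixed changes the question that the arm coefficient answers. Intention-to-treat compares everyone assigned to exercise with everyone assigned to control. The adjusted coefficient compares controls with one part of the exercise arm, chosen by behaviour after randomisation. At stake is the estimate for the outcomes that the abstract assigns to ANCOVA: it could miss a real benefit, misstate its size, or even reverse its sign.

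**Working it through.** **1. The protocol's own figure.** Inputs from the Sample Size section: 34 per group, difference 13.4, SD 16.67, two-sided 5%, two-group t test. The exact t calculation gives n = 33.5, so 34 per group, with power 0.904. The planned 68 reproduces. The unadjusted standard error is 16.67 × √(2/34) = 4.04.

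**2. What adjustment does under each coding of controls.** The protocol does not say how adherence is scored in the control arm, so the three natural choices are taken in turn.

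- *Controls coded non-adherent.* Only exercise participants can be adherent, so the arm coefficient compares controls with exercise participants who did not train.
- *Controls coded adherent* (they kept to no exercise). The arm coefficient compares controls with adherent exercise participants, which is a per-protocol contrast.
- *Controls left missing.* A complete-case ANCOVA loses the control arm.

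None of these is the intention-to-treat contrast.

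**3. Precision, controls coded non-adherent.** Let p be the share of the exercise arm above 40% adherence (an assumption; the protocol gives no expected rate). With 1:1 allocation the squared correlation of arm and adherence is (p/2)/(1 − p/2), and variance inflation is 1/(1 − that value).

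- p = 0.8: 0.4/0.6 = 0.67; inflation 3.0.
- p = 0.9: 0.45/0.55 = 0.82; inflation 5.5.

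The same result follows directly. At p = 0.8 the contrast rests on 34 × 0.2 = 6.8 exercise participants, and 16.67 × √(1/34 + 1/6.8) = 7.00 = 4.04 × √3.0. At p = 0.9 it rests on 3.4, and 16.67 × √(1/34 + 1/3.4) = 9.48 = 4.04 × √5.5. In simulation the mean standard errors were slightly larger, about 7.3 and 10.3, because the number of adherent participants varies from trial to trial.

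**4. Estimate and power, same coding.** Simulated trials (3,000 per scenario, 34 per arm, SD 16.67, true intention-to-treat difference 13.4), with adherence unrelated to prognosis:

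| Share of benefit through adherence | p | Adjusted arm estimate | Power, adjusted | Power, unadjusted |
|---|---|---|---|---|
| None | 0.8 | 13.5 | 45% | 90% |
| None | 0.9 | 13.5 | 29% | 91% |
| Half | 0.8 | 6.8 | 15% | 91% |
| Half | 0.9 | 6.9 | 10% | 90% |
| All | 0.8 | 0.1 | 5% | 88% |
| All | 0.9 | 0.0 | 5% | 89% |

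A separate run of 4,000 trials gave 46% and 28% for the first two rows, which agrees within simulation error. At p = 0.6 adjusted power was 67%, 24% and 5% for none, half and all.

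If people who would adhere also have better outcomes anyway (latent correlation 0.5), the adjusted estimate at p = 0.8 and 0.9 is 1.8 and −1.2 when none of the benefit runs through adherence, and −11.5 and −14.9 when all of it does.

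**5. Other coding.** With controls coded adherent, p is replaced by 1 − p in the formula. At p = 0.8 the squared correlation is 0.1/0.9 = 0.11 and inflation only 1.125. The precision cost is then small, but the target is still wrong: if all benefit runs through adherence, the coefficient is 13.4/0.8 = 16.75, not 13.4.

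**The case against.** The best reply is that the ANCOVA is not the only comparison. The repeated-measures ANOVA names no covariates, and the abstract analyses the effect on HAND by relative risk and absolute risk reduction. That stands. A reader might infer that the plan as a whole adjusts away the exercise effect; the text does not support this, and the defect is confined to the ANCOVA. It remains material there, because the abstract makes ANCOVA the estimator for quality of life and activity and participation.

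The second reply is that the figures depend on unstated inputs. This also stands. The coding of controls and the adherence rates are assumptions, and the Sample Size calculation is for an unadjusted t test on an outcome it does not name. The power losses illustrate the problem and are not the trial's planned power. That the estimand changes does not depend on these rates.

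Three further inferences are tempting but not supported:

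- *That follow-up cognition, CD4 count and viral load are adjusted for.* The Study Outcomes section says "These variables will be measured at baseline, after 12 weeks, and 3 months after the intervention", and baseline values are ordinary covariates. Only the time point is left open. The Neuropsychological Screening section also makes covariate use of the overall cognitive score conditional on need.
- *That the ovulation covariate drops men or duplicates sex.* A yes/no indicator does neither.
- *That all the listed covariates enter one model with 68 participants.* Simultaneous entry is not stated.

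**Conclusion.** The point holds for the two adherence covariates in the ANCOVA. Following the text as written gives an arm coefficient that is not the intention-to-treat effect, whichever way controls are coded, and this conflicts with the commitment in the same section.

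Complete removal of the effect is only one case. It needs controls coded non-adherent, all benefit running through the 40% threshold, and adherence otherwise unrelated to prognosis. In other cases the estimate is attenuated, biased or merely less precise. With controls coded non-adherent and 80% to 90% adherence in the exercise arm, power on the Sample Size inputs falls from about 90% to between about 46% and 5% when adherence is unrelated to prognosis. The lack of a stated time point for cognition, CD4 count and viral load is a lesser matter of wording.

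**What to change.** In the Statistical Methods section, delete exercise adherence and ART adherence since the intervention from the ANCOVA covariates, and stop calling exercise adherence a confounder in the Study Outcomes section. State that cognition, CD4 count and viral load enter only as baseline values, alongside other pre-randomisation covariates such as age, sex and education. Report both adherence measures descriptively by arm, or use exercise adherence in a separate, labelled supplementary analysis such as a complier-average effect.

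The sample size does not change. The main model adjusts for fewer variables, which is a small loss. The article reports that data analysis has not yet been carried out, so this is a change of wording, plus the notifications that the protocol requires for an amendment to the analysis.
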